#### Screening and enrollment procedure

In this study, pregnancy, GA and ownership of mobile phone will be used as the main selection and enrollment criteria. Hence, in the selected kebeles, first, all the reproductive-age women with a history of amenorrhea for the last 28 days, who do not use any family planning, and who own a mobile phone will be screened for pregnancy through beta-human chorionic gonadotropin (HCG) urine test. Then, the mothers who are found to be positive for the HCG urine test will be given a unique identification number (ID No) and screened for GA through their last menstrual period (LMP) and/or portable ultrasound (U/S) scan result. Next, those women of less than 16 weeks of GA will be registered as illegible for the study. Finally, for each control and intervention group, 320 pregnant women who fulfill the enrollment criteria will be selected by a simple random-sampling method (computer-generated random table) [23]. They will be registered with their ID No and mobile phone number on a computer tablet.

### Data collection method and tools

Data will be collected in three phases (phases I, II and III) using a questionnaire loaded on four computer tablets, and by four trained BSc nurses and six health extension workers (HEWs).

#### Phase I

In this phase, for both intervention and control groups, a baseline survey will be conducted on sociodemographic characteristics and maternal health care service use via a structured, interview-based questionnaire which will be adopted from similar studies. Maternal health status will be assessed through a medical interview checklist and nutritional status will be screened by using a mid upper-arm circumference (MUAC) tape, a weighing scale and a Hemacue machine or portable hemoglobin analyzers to test for hemoglobin level.

#### Phase II

This stage of data collection will be conducted after the eighth voice message or the fourth month of enrollment and the data collection will focus on maternal health condition, nutritional status and status of the voice messages which will be delivered to the intervention group, status of maternal health care service use among both intervention and control groups. During this period, data related to maternal health conditions will be collected through the same tools which will be used in phase I. In addition, data related to maternal health care services using status and voice message will be collected through a structured, interview-based questionnaire with confirmation of voice messages from their mobile phone.

#### Phase III

This phase of data collection will be done at study close-out and will be conducted after 24 voice messages or 45 days post delivery for every mother in the intervention and control groups. It will focus on maternal health condition, nutritional status, health care service use, pregnacy outcome and the status of the mobile-phone-based voice message since their enrollment time. Furthermore, mothers in the intervention group will be asked how voice messages helped them.

#### Intervention and follow-up procedures

This study will have two trial arms, “Trial arm A” is the intervention and “Trial arm B” is the control group.

#### Trial arm A

In this arm, a mobile-phone-based voice message consisting of information about the advantage of maternal health care service use (advantage of ANC, PNC and institutional delivery) and reminders of their appointment will be sent. Particularly, every 2 weeks a voice message composed of reminders for ANC follow-up and information about its advantages (first to fourth ANC visits) and expected date of delivery (EDD) will be sent. After birth, reminders for PNC follow-up (first to third PNC follow-up) and information about its advantages will be sent as voice messages through the mobile phone.

Published evidence supports the notion that the first ANC visit should be as early as possible in pregnancy, preferably in the first trimester (within the first 12 weeks of gestation) and in a normal pregnancy the protocol for pregnancy care recommends four ANC visits [24]. Hence, appointments for ANC follow-up will be adjusted based on GA with the first ANC visit preferably before 16 weeks of GA, otherwise at 16–24 weeks, the second ANC visit between 24–28 weeks, the third ANC visit between 28–32 weeks and the fourth ANC visit or last ANC visit between 32–40 weeks, preferably near to the EDD to ensure that the appropriate advice and care will be provided to prevent and manage problems such as multiple births (twins or more), post-maturity (which carries an increased risk of fetal death) and fetal mal-presentations. Therefore, based on the maternal enrollment framework criteria for this study, any mother with a GA of “*16 weeks-w*,” where “*w*” is any number of weeks less than 16, then the first voice message, which consists of reminders for the first ANC visit and information about advantage of this visit, will be sent. This voice message will be continued every 2 weeks until the end of the time frame for the first ANC visit which is 24 weeks of GA. Thus, a total of eight plus four voice messages will be sent as reminders for the first ANC visit and information about its advantages. Based on the time frame for the second ANC visit (24–28 weeks of GA), the 13th voice message from the initial message will be a reminder for the second ANC visit and information about its advantages. In this time frame, a maximum of two voice messages will be sent. The third stage of the voice message will be about reminders for the third ANC visit and its advantages. This stage of messaging will start from the 15th voice message and a total of two messages will be delivered. The last stage of voice messaging for ANC visit reminders and about its advantages will be started from the 17th voice message and this will consist of three parts (reminders for the fourth ANC visit, EDD and advantages of the fourth ANC and institutional delivery). A maximum number of voice messages from the date of enrollment and until the 42nd week of GA will be 21 voice messages. After the 21st voice message, the message will be changed to reminders for PNC follow-up and about its advantages. A total of three voice messages will be sent for PNC follow-up reminders and its advantages. Hence, an overall number of voice messages which will be sent for the intervention purpose will be 24. The content of all the messages will be first prepared in English and translated into the local language, “Afan Oromo,” and scripted to a female voice through a smart phone recording. Finally, these messages will be loaded on the mobile phone in voice message form to be sent regularly every 2 weeks at 7:00 a.m. to the intervention group:“Hello, this is voice message from a health center. How are you? We are sending this message to remind you about your first ANC visit. Maternal health care services are given free of any cost. This service will improve your health and your baby’s health. Please, come for your first antenatal care visit before 4 months (16 weeks), otherwise before 6 months (24 weeks) of your pregnancy. When you came for your first ANC service you will have a medical check-up, you will receive TT vaccine (medication that prevents tetanus from you and your baby), and you will also be given iron (element) and folic acid (medication which prevents anemia during pregnancy and promotes normal fetal growth). We are waiting for you to give free maternal health care services. If you have any problem please call to 09x……..”

*The above message will be sent to the intervention group in the form of a voice message for the first ANC visit.*
“Hello, this is voice message from a health center. How are you? We are sending this message to remind you about your second ANC visit. Maternal health care services are given free of any cost. This service will improve your health and your baby’s health. Please, come for your second ANC visit before 7 months (28 weeks) of your pregnancy. When you came for your second ANC you will have a medical check-up and your baby’s conditions will be checked. You will receive another dose of TT vaccine (TT2) (medication that prevents tetanus from you and your baby) and you will also receive other medical support based your health condition. Please, remember also that your Expected Date of Delivery/EDD is DD/MM/YY. We are waiting for you to give free maternal health care services. If you have any problems pleases call to 09x……..”

*The above message will be sent to intervention group in the form of voice message for the second ANC visit.*
“Hello, this is a voice message from a health center. How are you? We are sending this message to remind you about your third ANC visit. Maternal health care services are given free from any cost. This service will improve your health and your baby’s health. Please, come for your third ANC before 8 months (32 weeks) of your pregnancy. When you came for your third ANC, you will have a medical check-up for your baby’s condition and yourself. Please, remember also that your EDD is DD/MM/YY. We are waiting for you to give free maternal health care services. If you have any problem pleases, call to 09x…….”

*The above message will be sent to the intervention group in the form of voice message for the third ANC visit*
“Hello, this is a voice message from a health center. How are you? We are sending this message to remind you about your fourth ANC visit. Maternal health care services are given free from any cost. This service will improve your health and your baby’s health. Please, come for your fourth ANC before 10 months (40 weeks) of pregnancy or near to your EDD. When you came for your fourth ANC, you will have a medical check-up for your baby’s condition and yourself. Please, remember also your EDD is DD/MM/YY. We are waiting for you to give free maternal health care services. If you have any problem please call to 09x……”

*The above message will be sent to the intervention group in the form of voice message for the fourth ANC visit*
“Hello, this is voice message from a health center. How are you? We are sending this message to remind you about your postnatal visit. Maternal health care services are given free from any cost. This service will improve your health and your newborn baby’s health. Please, come for postnatal care (PNC). When you came for PNC, you will have a medical check-up for your newborn baby’s condition and yourself. Your baby will receive vaccine (medication that prevents babies from getting different diseases) and your baby’s growth status will be checked. We are waiting to give free maternal health care services. If you or your baby have any problem please call to 09x…..”

*The above message will be sent to the intervention group in the form of a voice message for PNC visit*

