**Methods/design:**

Through, a cluster-randomized controlled trial, 640 participants will be selected based on their districts and respective health centers as the unit of randomization. All pregnant mothers who fulfill the inclusion criteria will be allocated to a mobile-phone-based intervention and existing standard of care or control with a 1:1 allocation ratio. The intervention consists of a series of 24 voice messages which will be sent every 2 weeks from the date of enrollment until the close-out time. The control group will receive existing standard of care without voice messages. Data related to outcome variables will be assessed at three phases of the data collection periods. The primary outcome measures will be the proportion of antenatal care visits and institutional delivery, whereas the secondary outcome measures will consist of the proportion of postnatal care visits and pregnancy outcomes. Risk ratios will be used to a measure the effect of intervention on the outcomes which will be estimated with 95% confidence interval and all the analyses will be done with consideration of clustering effect.

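### Trial arm A gives two different triggers for the postnatal messages, and the fixed total of 24, on which the end-line and the sensitivity set rest, cannot be reached by 45 days after birth

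*Protocol article*

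**What the plan says.** All references are to the protocol article.

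- **PNC trigger, first statement (Trial arm A):** "After birth, reminders for PNC follow-up (first to third PNC follow-up) and information about its advantages will be sent as voice messages".
- **PNC trigger, second statement (same section):** "After the 21st voice message, the message will be changed to reminders for PNC follow-up and about its advantages". The sentence just before it gives 21 as the maximum number of messages between enrolment and 42 weeks of GA.
- **Stage numbers (same section):** "Thus, a total of eight plus four voice messages will be sent as reminders for the first ANC visit". The second-visit stage then starts at the 13th message counted from the initial one, the third-visit stage at the 15th, and the fourth-visit and delivery stage at the 17th. Three PNC messages follow.
- **Total:** "Hence, an overall number of voice messages which will be sent for the intervention purpose will be 24". The abstract repeats it as "a series of 24 voice messages which will be sent every 2 weeks from the date of enrollment until the close-out time".
- **Entry:** GA must be below 16 weeks (Participants: inclusion and exclusion criteria). Women are screened only with a "history of amenorrhea for the last 28 days" and then need a positive HCG urine test (Screening and enrollment procedure).
- **Phase II** "will be conducted after the eighth voice message or the fourth month of enrollment", so the count runs from enrolment.
- **Phase III** "will be conducted after 24 voice messages or 45 days post delivery for every mother in the intervention and control groups". Primary outcome measures offers the 24th message or study close-out. The Analysis plan section gives only the 24th message.
- **Sensitivity set (Sensitivity and per-protocol analysis):** participants who completed the follow-up of the 24th message.
- **Controls** receive no voice messages, and deliveries are tracked by fieldworkers and health professionals (Control arm B). PNC use means at least one PNC follow-up, within 45 days or 6 weeks of birth (Secondary outcomes).

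**The concern.** A birth trigger and a message-count trigger agree only if the 21st message happens to fall at about the time of delivery. If it does not, field staff have two instructions and must choose one.

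Following the count would send antenatal scripts late or after delivery, and would send PNC reminders after the period in which PNC use is measured. Following birth makes the promised 24 messages unattainable, although the Analysis plan and the sensitivity analysis are both worded around the 24th. In either case a message count cannot time the end-line of a control woman or decide whether she belongs in the sensitivity set.

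**Working it through.** **Inputs.** Messages go out every 2 weeks from enrolment. Entry GA is g, from 4 weeks (28 days of amenorrhea, GA counted from the last menstrual period) to 15 weeks 6 days. Birth is at GA B. I take B as 37, 40 and 42 weeks; 42 is the limit the protocol itself uses, and the others are illustrative. The PNC window is 45 days.

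**Formula.** Message k falls at GA g + 2(k − 1).

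**Reproducing the protocol's numbers.**

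- First message at GA 2: messages up to and including week 24 = (24 − 2)/2 + 1 = 12. Messages 13, 15, 17 and 21 fall at weeks 26, 30, 34 and 42. All stages fit, and 21 + 3 = 24.
- First message at GA 0: 12 messages fall before week 24, and messages 13, 15, 17 and 21 fall at weeks 24, 28, 32 and 40. This also fits.
- First message at GA 4, the earliest eligible entry: 11 messages by week 24, message 21 at week 44, and only 20 messages by week 42.

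So the numbering works for a first message at GA 0 to 2 weeks, which the screening rule excludes.

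**Reading 1: PNC messages triggered by birth.** Total = floor((B − g)/2) + 1 + 3.

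| Entry g (weeks) | B = 37 | B = 40 | B = 42 |
|---|---|---|---|
| 4 | 20 | 22 | 23 |
| 8 | 18 | 20 | 21 |
| 12 | 16 | 18 | 19 |
| 15 | 15 | 16 | 17 |
| 15w6d | 14 | 16 | 17 |

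The range is 14 to 23. A total of 24 needs 21 messages by birth, that is B ≥ g + 40, or 44 weeks even for entry at week 4.

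**Reading 2: the count followed literally.** Message 13 falls at g + 24, message 17 at g + 32, message 22 (the first PNC message) at g + 42 and message 24 at g + 46.

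| Entry g (weeks) | GA of message 13 | GA of message 17 | Message 22, days after 40-week birth | Message 24, days after 40-week birth |
|---|---|---|---|---|
| 4 | 28 | 36 | 42 | 70 |
| 8 | 32 | 40 | 70 | 98 |
| 12 | 36 | 44 | 98 | 126 |
| 15 | 39 | 47 | 119 | 147 |
| 15w6d | 39w6d | 47w6d | 125 | 153 |

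- A PNC message arrives within 45 days only if 7(g + 42 − B) ≤ 45. For B = 40 this means g ≤ 4.4 weeks; for B = 42, g ≤ 6.4 weeks; for B = 37, g ≤ 1.4 weeks, so no eligible woman.
- For entry at week 12, the second-visit reminder (window 24 to 28 weeks) goes out at week 36.
- For a 40-week birth and entry after week 8, the stage that covers institutional delivery starts after delivery.
- After a 40-week birth, message 24 comes 25 to 108 days later than a 45-day end-line (70 − 45 and 153 − 45).

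**Common to both readings.** In the best case (g = 4, B = 42), two-weekly messages up to 45 days after birth number 23; message 24 falls at GA 50, day 56.

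**The case against.** The strongest reply is that the protocol means GA and birth throughout. It calls 21 a maximum, gives each antenatal visit a GA window, adjusts appointments to GA, puts each woman's expected delivery date in the scripts and tracks deliveries. On that view the 21st message simply stands for the end of the longest pregnancy, and the 24 is one message too high in the best case. Phase III also offers 45 days post delivery for every mother in both arms, which is a workable end-line.

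Much of this stands. GA and birth sending is a plausible intention, and the postpartum delays in the second table arise only if staff follow the count. But the intention does not rescue the text. The overall number is stated as what will be sent, not as a ceiling; the stages are numbered from the initial message; and Data quality control reschedules disrupted messages without reducing their number. The Analysis plan drops the 45-day alternative.

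Three stronger inferences are tempting but not supported:

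- **That the 24 messages cannot be delivered at all.** On the literal count they can, only too late.
- **That the sensitivity set is empty.** The phrase about the 24th-message follow-up may just be a label for phase III, in which case the set is the completers and needs only clearer wording.
- **That the end-line is unworkable.** Phase III already contains a usable rule.

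**Conclusion.** The point holds as an internal inconsistency that should be corrected. Two triggers are given for PNC messages, and the stage numbers fit no eligible entry GA. Birth-triggered sending yields about 14 to 23 messages; literal counting puts the first PNC message about 6 to 18 weeks after a 40-week birth, outside the 45-day window for nearly all women. The Analysis plan's end-line and the sensitivity set are therefore worded around a count that is unattainable by 45 days post delivery and undefined for controls.

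This rests on GA counted from the last menstrual period, entry at 4 weeks or later, birth at 37 to 42 weeks and the stated 2-week interval. Sample size and power do not change. The PNC trigger itself bears on a secondary outcome; only literal use of the stage numbers would also displace antenatal and delivery reminders.

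**What to change.** 1. In Trial arm A, choose the antenatal script by the woman's current GA, using the windows already given there.
2. Send the three PNC messages at the next 2-week slots after the tracked birth. With the first slot within 14 days of birth, the third falls by day 14 + 28 = 42, inside the window.
3. State the stage numbers as maxima and replace the fixed 24 with *all messages due* (about 14 to 23), in the abstract as well.
4. In Phase III, Primary outcome measures and the Analysis plan, use 45 days post delivery as the single end-line rule in both arms.
5. Define the sensitivity set as women with completed phase III follow-up, by the same rule in both arms. Do not add a messages-received condition for the intervention arm: that would select on adherence after randomisation in one arm only and bias the comparison.

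The cost is a GA and birth status column in the sending list plus these text edits; delivery tracking already exists. The number of messages will vary between women, and birth reports must reach the list within about 2 weeks. One missed slot moves the third PNC message to as late as day 56.

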#### Control arm B

Participants in the control group will receive existing SOC which informs them about the advantages of maternal health care service use at HCs, informing them about the service which is given free of charge and giving appointments for regular follow-up. Unlike the intervention group, however, these participants will not be sent the voice message to remind for appointment and information about the advantage of maternal service use. With regards to the data collections, a house-to-house survey will be made among the households which will be identified with pregnant mothers who fulfill the inclusion and enrollment criteria. The three phases of the survey (I, II and III) will be made to collect data from the mothers who are in the trial. The survey will focus on maternal socio-demographic status, maternal health conditions, nutritional status, and health care service use and pregnancy outcome. The data collection tools will be the same for both trial arms (Trial arms A and B), except for mobile-phone-based voice message status.

For either intervention or control group if the study participants move from the study area before the study is completed, or withdraw from the study before the final data collection period, they will be registered as dropouts to follow-up.

Assuming that all mothers may give birth at different GAs their status of delivery will be tracked by fieldworkers and health professionals at selected HCs (Fig. 2).

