### Participants: inclusion and exclusion criteria

The participants will be recruited from two districts (Haramaya and Kombolcha districts) based on pre-set eligibility criteria (pregnancy, gestational age (GA), ownership of a mobile phone and willingness to participate). The participant will be included in the trial if her GA is less than 16 weeks, she owns a mobile phone and has willingness to participate. The potential trial participants will be identified by the field worker-based enrollment criteria. For all eligible participants, the field workers will explain about study by reading the participant information sheets; if the study subjects are willing to participate, written informed voluntary consent will be obtained and baseline data collection will be made.

In this trial, study women who fulfill the enrollment criteria for the study but are critically ill at time of enrollment will be excluded from the study. Critically ill women are those pregnant mothers who unable to respond to interview questions because of illness. In addition, women with any systemic illness during this time will be excluded from the study. Any pregnant women with systemic illness need an special ANC follow- up, which is different from the recommended routine ANC follow -up and this set precondition without effect of treament for good adherence to maternal health care service use. Hence, any pregnant mother with known systemic illnesswill be excluded from this study.

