### Operational definitions

*Mobile-health* **=** the use of a mobile phone to support health care at individual, community or systems level*Maternal health care service utilization* **=** the women’s health care service use from conception to delivery and during postnatal period till 45 days or 6 weeks*Antenatal care service use* **=** maternal health care service use during pregnancy*Institutional delivery* **=** giving birth in health facilities*Postnatal care service use* = maternal health service use after birth within 45 days*Pregnancy outcome* ***=*** the final result of a fertilization event such as live birth (full-term or preterm birth), stillbirth, spontaneous abortion and induced abortion*Adverse pregnancy outcome* = includes maternal adverse outcomes and/or neonatal adverse outcomes*Maternal adverse outcome* = maternal illness or maternal near miss and/or maternal death*Neonatal adverse outcome* = neonatal morbidity and/or neonatal mortality*Stillbirth* **=** any fetus born at 28 weeks of gestational age or more with no heart beat or respiratory effort*Low birth weight* **=** birth weight less than 2500 g after viability*Preterm* **=** any birth occurring between 28 and 37 weeks of gestation*Abortion* **=** the termination of pregnancy before 28 weeks of GA*Maternal near miss* **=** a woman who nearly died but survived a complication that occurred during pregnancy, childbirth or within 45 days of termination of pregnancy*Maternal mortality* **=** the death of women during pregnancy or within 45 days of termination of pregnancy irrespective of the duration from any cause related to, or aggravated by, the pregnancy or its management but not from accidental or incidental causes*Neonatal mortality* **=** the death of infants with in the first 28 days of life*Institutional delivery* = child-birth attended by skilled health professionals*Maternal under-nutrition* **=** mother will be considered as undernourished if she has anemia and/or wasting or/and underweight or low weight-gain during pregnancy*Anemia* **=** mother will be considered as anemic if the level of hemoglobin is less than 11 g/dl which will be measured through the Hemocue machine*Severe anemia* = mother will be considered to have severe anemia if the level of hemoglobin is less than 7 g/dl which will be measured through Hemocue machine*Wasting* = mother will be considered to have wasting if the MUAC measurement is less than 18.5 cm*Underweight* = mother will be considered as underweight if her Body Mass Index (BMI) is less than 18.5 kg/m^2^

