#### Primary outcome measures

This study has two primary outcomes (proportion of ANC use and institutional delivery). The assessment of outcome measures will be conducted starting from phase II data collection time (after the eighth voice message or 4 months from the date of enrollment) and at phase III data collection time (after the 24th voice message or at close-out time off study). All the participants in the trials will be interviewed about their ANC visits and place of delivery by using a structured questionnaire. Antenatal care service use is defined as maternal health care service use during pregnancy. The participants will be considered as an ANC service user if they have at least one ANC visit. Institutional delivery is giving birth at a health facility (Fig. 3).

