#### Secondary outcomes

The secondary outcome measures consist of PNC service use and pregnancy outcomes. Postnatal care service use is a maternal health care service use after birth within 45 days or 6 weeks. The participants will be considered as a user of PNC services if they have at least one PNC follow-up. Pregnancy outcome is the final result of fertilization events such as a live birth (full term or preterm), still birth, spontaneous abortion or induced abortion, low birth weight and normal birth weight. All the participants of this trial will be interviewed for the secondary outcome at phases II and III data collection time. To assess secondary outcome measures, a structured, interview-based questionnaire, which includes a status of PNC follow-up and pregnancy outcome, will be used.

For both primary and secondary outcome measures, participants’ medical record will be used for cross checking to avoid social desirability effects during the interview (Fig. 3).

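### Women who move away are registered as dropouts with no stated attempt to reach them on their registered phone, then scored as non-users; with one district per arm, unequal migration biases the comparison

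*Protocol article*

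**What the plan says.** The rule on leaving the trial stands under Control arm B but is worded for both groups: "if the study participants move from the study area before the study is completed", or if they withdraw before the final data collection, "they will be registered as dropouts to follow-up". The article describes no contact with such women afterwards.

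Other sections bear on this rule:

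- **Phone on file.** A woman is eligible only if "she owns a mobile phone and has willingness to participate" (Participants: inclusion and exclusion criteria). Of the women selected for either group, Screening and enrollment procedure says: "They will be registered with their ID No and mobile phone number on a computer tablet".
- **Outcome source.** "All the participants in the trials will be interviewed about their ANC visits and place of delivery by using a structured questionnaire" (Primary outcome measures). Secondary outcomes says: "All the participants of this trial will be interviewed for the secondary outcome at phases II and III data collection time". That section also has medical records checked against the interview, for primary and secondary outcomes alike. Control arm B adds that fieldworkers and staff of the selected health centers follow each woman's delivery status.
- **Missing outcomes.** Under the intention-to-treat rule for the primary outcomes (Analysis plan), a woman lost to follow-up whose service use is missing at close-out is counted as not having used the service.
- **Arms.** Haramaya district is the intervention arm and Kombolcha the control arm, with one health center selected in each (Randomization and sampling procedure).
- **Sample size.** 320 women per arm, with no stated allowance for dropout (Assumption and hypothesis for sample size calculation).

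**The concern.** A woman who moves has not withdrawn consent, and her outcome still exists. Institutional delivery is defined as birth in a health facility, with no restriction to facilities in the study area, so a facility birth after a move meets the definition. The items needed are short: whether she had at least one antenatal visit, and where she gave birth. A call to the registered number could obtain them.

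Read together, the two rules do more than lose data. The follow-up rule creates the missing value and the analysis rule turns it into a failure. If migration were the same in both districts, this would lower both proportions and cost power. If it differs, the comparison itself shifts. Because each arm is a single district, nothing in the design can separate a migration difference from a treatment effect. The planned sensitivity analysis keeps only women followed through the 24th message, so it would leave movers out, not recover their outcomes.

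**Working it through.** **Inputs from the article.** Institutional delivery 47% (control) and 60% (intervention); two-sided 5% level; 80% power; design effect 1.3; 320 per arm. **Assumed, because the article gives no rate:** the share *d* of women who move and have no close-out outcome, taken from 5% to 20%. Every such woman is scored as a non-user, as the Analysis plan requires.

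**1. The plan's own figure.** The two-proportion formula for 47% v 60% gives 230 per arm without continuity correction and 246 with it.
- 230 × 1.3 = 299
- 246 × 1.3 = 319.8, rounded up to 320

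The continuity-corrected form reproduces the stated 320. Nothing is left in it for dropout.

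**2. How many women.** At *d* = 10%, 0.10 × 640 = 64 women.

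**3. Equal migration.** Observed proportion = true proportion × (1 − *d*). Effective size per arm = 320 / 1.3 = 246. Power is computed without continuity correction, which is why it starts above 80%.

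| *d* in both arms | Control | Intervention | Power |
|---|---|---|---|
| 0% | 47.0% | 60.0% | 82.6% |
| 5% | 44.7% | 57.0% | 78.4% |
| 10% | 42.3% | 54.0% | 74.0% |
| 15% | 40.0% | 51.0% | 69.3% |
| 20% | 37.6% | 48.0% | 64.6% |

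The risk ratio stays at 0.60 / 0.47 = 1.28. The loss is in power and in the risk difference.

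**4. Unequal migration, no true effect (47% in both arms).** Observed risk ratio = (1 − *d* intervention) / (1 − *d* control).

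- 5% in one arm, 15% in the other: 0.47 × 0.95 = 44.7% and 0.47 × 0.85 = 40.0%. If more women move in the intervention district, the ratio is 0.85 / 0.95 = 0.89. If more move in the control district, it is 0.95 / 0.85 = 1.12.
- 5% and 10%: 0.90 / 0.95 = 0.95, or 0.95 / 0.90 = 1.06.
- 10% and 20%: 0.80 / 0.90 = 0.89, or 0.90 / 0.80 = 1.13.

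In the first case the spurious difference is 44.65 − 39.95 = 4.7 percentage points. That is 4.7 / 13 = 36% of the difference the trial is sized to detect.

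**5. Unequal migration, planned effect true (47% v 60%).**
- 5% control, 15% intervention: 0.60 × 0.85 = 51.0% against 44.7%, ratio 1.14.
- 15% control, 5% intervention: 0.60 × 0.95 = 57.0% against 40.0%, ratio 1.43.

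The planned ratio is 1.28.

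**The case against.** The strongest objection is that being registered as a dropout is a participant-flow label. It neither forbids tracing nor says that data already collected are deleted. Tracing procedures are ordinary content of a full protocol or field manual, neither of which is shown. Antenatal use needs only one visit and is assessed from Phase II, so a woman who moves after Phase II may already have that outcome recorded. The migration rates are assumptions, and the bias arises only because of the non-user rule.

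Much of this is fair. The size is conditional, and it applies mainly to place of birth. But the point concerns a rule the article does state, namely that moving is handled in the same way as withdrawal. A tracing procedure elsewhere would have to be reconciled with it. The dependence on the non-user rule is part of the point, because the two rules act in sequence.

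A reader might also infer two stronger claims, and the article supports neither.

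- *That outcomes come only from interviewing the woman.* Medical records are used as a cross-check and delivery status is tracked locally. These sources could show a delivery at a selected health center. They help little once a woman has left, since the tracking is tied to those centers and the records are described as a check on an interview, not a replacement for one.
- *That maternal deaths are lost by rule.* The dropout rule covers moving and withdrawal, not death. Maternal death appears under Operational definitions but not among the listed primary or secondary outcomes.

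**Conclusion.** The point holds for women who move, and only for them. The article registers them as dropouts alongside women who withdraw, states no attempt to use the phone number it holds for each, and counts those with missing close-out service use as non-users. A facility birth after a move is scored as a failure.

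Under an assumed 5% v 15% migration and no true effect, 47% in both arms becomes 44.7% v 40.0%, a risk ratio of about 0.89 or 1.12 by direction. With equal migration of 5% to 20%, power falls from 82.6% to between 78.4% and 64.6%. These figures take the design effect of 1.3 at face value and assume that no mover's outcome is found by other means. If few women move, or equally few in each district, the effect is small. The article gives nothing from which to judge that, so this is a worthwhile and inexpensive improvement, not a fatal flaw.

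**What to change.** Change the rule under Control arm B so that only withdrawal of consent ends follow-up. For women who move, take the Phase II and Phase III outcome items (antenatal visits, place of birth, postnatal care, pregnancy outcome) by phone on the registered number. Use the same procedure in both arms and the existing data collectors. The non-user rule would then apply only to women who could not be reached. Report by arm how many moved and how many were reached.

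The cost is a change of wording and a limited number of calls. There are two downsides. Phone reports from women who have moved may lack the medical-record check that guards against social desirability. Response to calls may also differ by arm, because the phone is the channel of the intervention. Both are handled by flagging these reports and repeating the analysis without them.
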